#### Facilitation

Facilitation (Table 3) is based on the Integrated-Promoting Action on Research Implementation in Health Services Framework [73] and promotes provider self-efficacy [74] in mitigating organizational barriers to EBP adoption. Facilitation is delivered via regular phone contact for at least 10 weeks with the SPs by an expert in school and mental health care organization, implementation methods, and use of CBT and EBPs in schools. The facilitator will support SPs in strategic thinking and leadership skills to address organizational barriers covering the following:Initiation and benchmarking (week 1): facilitator contacts each SP to give background on CBT, review potential barriers and facilitators to CBT use (e.g., space to provide CBT, school administration support for the program), and set measurable goals for CBT uptake.Mentoring (weeks 2–9): facilitator and SP hold regular weekly calls to develop rapport; facilitator provides guidance to SP on overcoming specific barriers to CBT uptake by aligning SP strengths with SP available influence at the school and needs of local staff. If needed, facilitator refers SP to REP technical assistant (TA).Leveraging (weeks 2–10): facilitator continues calls with SP and reaches out to school administrators, identifies school/community priorities per administration input, and helps SP align CBT use/goals with these existing priorities. The facilitator helps SP summarize and describe added value of CBT to administrators and other school employees (e.g., consistency with other initiatives).Ongoing marketing (continuous): facilitator, leadership, and SP summarize progress and develop sustainability plans.

**Table 3 Tab3:** Data sources and measures*

Primary aim:	Measures	Measure frequency	Data sources
Primary outcome and endpoint	Total number of sessions of CBT delivered over the course of 18 months	Weekly, months 1–18 (no collection during summer months)	SP weekly survey
Secondary outcomes	Full sessions of CBT delivered; non-group CBT sessions delivered; brief sessions (< 15 min) of CBT delivered; CBT components delivered	Weekly, months 1–18 (no collection during summer months)	SP weekly survey
Exploratory outcomes	Student mental health outcomes (PHQ-9T; GAD-7)	Months 3, 6, 12, and18	Student survey administered by SP
	Student knowledge of CBT; reported CBT receipt	Months 3, 6, 12, and 18	Student survey administered by SP
Exploratory aim 1: cost effectiveness	Cost of REP, coaching, and facilitation	Weekly, months 1–15; Daily during 2-week time and motion survey	Coach and facilitator logs; REP TA database; SP time and motion survey
	School outcomes (attendance, graduation, GPA); Health services (referrals to care; emergency department admissions)	Student baseline, 6, 12, and 18 months	Student survey administered by SP; academic indicators survey
Exploratory aim 2: moderators	School factors: size, % of students eligible for free/reduced lunch; school administrator support	Baseline	School administrator survey
	SP factors (aggregated): Baseline (run-in): Perceptions of CBT, prior training; time-varying (phase 2): Satisfaction with Phase 1 implementation support, CBT delivery during phase 1, reported barriers to CBT	Baseline, weekly	SP weekly survey; SP survey
Exploratory aim 3: mechanisms	Knowledge, perception, skills, barriers to use; EBPAS, ICS, ILS	Baseline, months 3, 6, 12, and 18	SP survey
	School contextual factors; ILS	Baseline, month 18	School administrator survey
Covariates	Student demographics/behaviors; access to mental health services	Months 3, 6, 12, and 18	Student survey administered by SP
	School factors (attendance, graduation, rates, GPA)	Baseline, month 18	School administrator survey, Academic indicator assessment

**CBT* cognitive behavioral therapy, *SP* school professional, *PHQ-9T* Patient Health Questionnaire 9-item Survey for Teens, *GAD-7* Generalized Anxiety Disorder 7-item survey, *REP* Replicating Effective Programs, *EBPAS* Evidence-Based Practice Attitude Scale, *ICS* Implementation Climate Scale, *ILS* Implementation Leadership Scale

### Fidelity monitoring to implementation strategies

Fidelity monitoring will be used to assess whether each site is receiving the core components of each implementation strategy (REP, coaching, and/or facilitation) and to ensure that there is no contamination. Different staff members will serve as REP specialists, coaches, and facilitators. Study staff will train REP specialists, coaches, and facilitators, and meet with them on a regular basis to monitor fidelity. Separate study staff will oversee monitoring of implementation strategy fidelity. Fidelity metrics are described in detail in Table 2. Adequate fidelity to REP is defined by all sites receiving the CBT package, > 90% of SPs receiving training, and at least one monthly contact by the TA specialist to SPs. For coaching, a fidelity checklist [75] will document content covered, post-session feedback provided, session planning and role-play practice that occurred, and provision of resources and materials. The facilitation quantitative fidelity measure [34, 76, 77] will ascertain mode of contact, general content of discussion, and interaction time [39].

### Measures

Data sources and measures (Table 3) will ascertain frequency of CBT session delivery by SPs through month 18 (primary outcome), school-level factors (administrator survey), SP characteristics, and a student outcomes survey. Independent study research associates (RAs) will collect all assessments from SPs and school administrators electronically. To protect student anonymity over the course of the study, SPs themselves will facilitate administration of student surveys, also collected electronically via a secure server that immediately de-identifies all student information.

#### Aim 1 primary outcome (CBT delivery)

The *primary outcome* is the total number of CBT sessions delivered by each SP to students over the course of 18 months. To assess this outcome, SPs will complete a weekly survey where they report their weekly CBT delivery in group or individual sessions, as well as the compnents delivered.  Secondary outcomes will include different types of CBT delivery (individual vs. group; full sessions vs. brief) and delivery of specific CBT components. SPs will be compensated for weekly survey completion in the registry, and study staff will follow up with SPs who do not report CBT delivery for 4 weeks in order to remind them to complete data entry.

#### School-level measures

A longitudinal survey will be given to consenting school administrators to record percentage of students eligible for free/reduced lunch, average classroom size, attendance rate, number of students referred to psychiatric emergency services, and administrator tenure. Administrators will also complete the Implementation Leadership Scale (ILS) [78] to assess institutional support for EBP. No identifying information will be collected as part of these assessments, and no compensation will be provided. Administrators will also be asked to provide approval for participating SPs to collect academic indicator data on GPA, absences, suspensions, and expulsions for participating students.

#### SP characteristics

SPs will also complete longitudinal web-based surveys that include demographic background, level of education, job tenure, prior experience administering CBT, and knowledge and perceptions of CBT delivery using the CBT Knowledge Questionnaire [79]; Provider Attitude Survey [80]; Treatment Manuals Survey [81]; and the Psychotherapy Practice Scale [82]. SPs will be compensated for all completed assessments. SPs will also complete the ILS to ascertain leadership support, and two other validated measures related to support for EBPs—the Implementation Climate Scale (ICS) [83] and the Evidence-Based Practice Attitude Scale (EBPAS) [84].

#### CBT fidelity

Consistent with real-world fidelity monitoring for quality improvement purposes [85], the abovementioned web-based SP weekly assessment will be used to track number of CBT sessions delivered and CBT content delivered each week.

#### Student outcomes

SPs wil be encouraged to identify 10 students that they believe could benefit from CBT prior to and during CBT training. SPs will be trained to create a mini-registry of students using a web-based instrument designed by TRAILS to communicate with other Qualtrics surveys (see Additional file 2: Appendix 2). Students identified by the SP will complete secure electronic surveys on mental health symptoms and health care utilization using the previously described web-based tool (Table 3). SPs will provide to the student in person an information sheet outlining the study eligibility requirements, assessments, compensation, and risks and benefits. A waiver of documentation of consent and waver of parental consent was obtained for ascertaining student outcomes from local IRBs. SPs will be required to provide students with a private location for completing all assessments and will reassure students prior to each assessment that all answers will be de-identified and that they will not have access to the responses. Measures will include student sociodemographic characteristics, health behaviors (e.g., substance use), CBT receipt, knowledge, and use of CBT skills, mental health symptoms (PHQ-9T, GAD-7), and access to mental health services and other healthcare use (e.g., ED referrals or admission). To ensure that students are not coerced into participation, they will be asked to confirm on the web-based survey that they would like to submit their answers. SPs will not be informed if students opt to not submit their answers after completing the survey. Students will be compensated for each survey completed over the 15-month period. In order to protect student privacy from the study staff, SPs will facilitate all student compensation.

#### Cost estimates

For each implementation strategy, we will calculate the average costs and average outcomes per SP using methods described elsewhere [39]. The primary implementation costs are the personnel time spent in REP activities (e.g., SP training, TA), coaching (e.g., time to hire/train coaches, network maintenance, SP coaching time), and facilitation by study participants (including SP and school administrator time). Costs will be quantified as hours multiplied by wages and fringe benefits for each person. Wage rates will be obtained from school records, and in cases where this information is not available, average wages for each occupational level will be used from the Bureau of Labor Statistics. Hours will be tracked through attendance logs for each implementation activity.

To assess costs of delivering CBT, 40 randomly selected SPs will also be asked to complete time-motion surveys for 2 weeks (starting 4 weeks after the phase 2 randomization) that ask about time allotted to providing CBT versus other forms of student counseling, care, or crisis management. School services will be translated to costs based on the wage rates of school providers.

Student-level service costs of CBT delivery and other use will also be estimated from study records of participation in CBT sessions, academic indicators, and self-reported utilization survey data on inpatient, emergency department, and outpatient use outside the school setting. Health care costs will be assigned using Current Procedural Terminology (CPT) codes, and a relative value unit (RVU) weight in the Medicaid Fee Schedule calculates standardized costs in US dollars for each service adjusted for annual levels of inflation using the consumer price index.

### Study sample retention

We will aim to prevent study attrition by following a planned protocol for obtaining the primary research outcome (total CBT sessions delivered by each SP), even if a SP moves to another institution (occurring among < 2% of SPs in our previous studies). A study research assistant (RA) will monitor SP weekly reports of CBT delivery. SPs who fail to submit reports for four consecutive data collection waves will receive two personalized emails from the study RA asking for their report. SPs who do not respond will be contacted by phone by study staff. Study staff will maintain brief communication with all SPs through periods of vacation and will provide easy methods for reporting job transitions that could impact data collection.

### Analyses

All eligible schools, once consented and randomized at phase 1, will be included in an intent-to-treat data analysis sample for all aims. Analyses of student mental health outcomes, however, will be restricted to schools in which at least one SP provided a list of student names for study participation prior to the first randomization. A detailed analysis plan is available in Additional file 3: Appendix 3.

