### Study design

Figure 1 details the four phases of this study over an 18-month period; the four phases are 3, 2, 10, and 3 months in duration, respectively.

The run-in phase involves deployment of the REP implementation strategy (CBT manual package, training, and technical assistance) and identification of schools, SPs, and potential students in need of CBT by SPs.

For phase 1, eligible schools are randomized with equal probability to continued REP only versus REP combined with coaching (REP+coaching). At the end of phase 1, schools are assessed to determine whether they would potentially benefit from facilitation.

During phase 2, schools that could benefit from facilitation [39] (see Additional file 1: Appendix 1) will be re-randomized in phase 2 with equal probability to continue their implementation strategy from Phase 1 (i.e., REP or REP+coaching) or to have their current strategy augmented with facilitation (i.e., REP+facilitation or REP+coaching+facilitation, respectively). The active elements of the coaching and facilitation strategies will be paused during the summer months (June–August 2019) when schools are not in session.

For phase 3, all implementation strategies will be discontinued. Outcomes will be collected longitudinally throughout all phases, from SPs up to 18 months after the baseline assessment and from students up to 15 months after their baseline assessment.

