### Student eligibility and recruitment

As part of REP, SPs will be trained during the run-in phase to identify 10 eligible students in need of CBT. Because accurate case finding is critical to successful CBT implementation, training SPs on student identification is a core component of the REP implementation strategy [39] used in previous studies of implementation strategies [40, 50]. SPs will be taught through REP to recognize signs of depression and anxiety in students, using public domain screens (Patient Health Questionnaire 9 modified for teens [PHQ-9T] and generalized anxiety disorder [GAD]-7) [51].

Students are considered eligible if the SP determines they have at least one symptom of depression or anxiety that impacts their daily functioning and well-being. Students are considered ineligible as determined by the SP if they are (1) high school seniors (or would be graduating prior to any CBT sessions); (2) are unable to regularly attend school-delivered CBT skills groups; or (3) are unlikely to benefit from CBT skills groups due to cognitive or developmental disability, lack of English proficiency, or significant behavioral difficulties.

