#### Coaching

The coaching implementation strategy (Table 2) is provided by TRAILS clinicians and is derived from the school-based Positive Behavior Interventions and Supports (PBIS) model of coaching for individual development [65]. Coaching uses a CBT training expert to attend in person to observe group sessions led by the SPs, provide live feedback [66, 67], and model the use of core CBT elements to improve SP competence [65, 68–72]. All SPs from schools randomized to coaching in phase 1 will receive weekly visits from a CBT coach for a minimum of 12 weeks, which will occur in the context of the SPs weekly CBT group. After 12 weeks of on-site coaching, SPs are evaluated on their CBT skill delivery through a short objective competency quiz. SPs deemed to need a full second round of coaching based will receive another full 12 weeks of coaching.

**Table 2 Tab2:** Fidelity checklist summary for REP, coaching, and facilitation components

Implementation step	Specific implementation tasks	Date completed	Summary of fidelity measure for each component
REP	Step 1: identify schools and SPs, market CBT program		# SP names and contacts, marketing reach (# web hits)
	Step 1: DM disseminates SP and school administrator baseline surveys		# completed surveys
	Step 1: TS orients and trains SPs to use web tool to track all CBT encounters		# SPs at schools receiving package, # website visits
	AN randomizes eligible sites to REP or REP+coaching—phase 1		Complete phase 1 randomization
	Step 2: TS holds training (1 day)		# SPs trained
	Step 2: DM receives list of 10 students/SP		# students listed at each site
	Step 3: TS with TA begin virtual CBT technical assistance phase via regular calls		Call date with SPs, # CBT sessions/site
	Step 3: DM monitors SP uptake of CBT at schools via web tool		# students identified at each school, # CBT sessions
	Step 3: DM starts student assessments		# student assessments completed
	Step 3: TA disseminates school-specific uptake monthly report, eligibility survey		# monthly reports disseminated to each school
	AN determines if site would benefit from facilitation		
	AN randomizes sites that might benefit to add facilitation or not—phase 2		Complete phase 2 randomization for schools that might benefit from facilitation
	Step 3: TA holds as-needed calls with SPs upon request regular conference calls		# conference calls held and attendance
	Step 3: TA sends out regular newsletter highlighting CBT success stories		# newsletters disseminated

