### Trial status

The study has not started as of August 2018. In the run-in phase (October 2018–January 2019), all eligible SPs will receive Replicating Effective Programs (REP) components, including a 1-day didactic training in CBT in mid-January of 2019. The first randomization will occur in late January 2019.

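### The pre-randomization listing condition for the student outcome analyses is set per school, so the stated rule does not exclude students listed after allocation; Table 2's row order also conflicts with the dated timeline

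*Protocol article*

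**What the plan says.** Under Analyses, the protocol article says that all eligible schools, once consented and randomized in phase 1, "will be included in an intent-to-treat data analysis sample for all aims". It then makes one exception. Analyses of student mental health outcomes are "restricted to schools in which at least one SP provided a list of student names for study participation prior to the first randomization". The article states no condition at the level of the SP or the student, and refers to Additional file 3, Appendix 3, for the detailed analysis plan.

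On the timing of student identification, the text is consistent:

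- Study design: the run-in includes "identification of schools, SPs, and potential students in need of CBT by SPs".
- Student eligibility and recruitment: "SPs will be trained during the run-in phase to identify 10 eligible students in need of CBT".
- Student outcomes: SPs are "encouraged to identify 10 students that they believe could benefit from CBT prior to and during CBT training".
- Trial status: the run-in has SPs receiving REP components, "including a 1-day didactic training in CBT in mid-January of 2019", with the first randomization in late January 2019.

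Table 2, the fidelity checklist, has a different order. The row "AN randomizes eligible sites to REP or REP+coaching—phase 1" comes first, then the 1-day training, then "Step 2: DM receives list of 10 students/SP", then the start of student assessments.

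**The concern.** In a cluster-randomized trial, participants chosen after the cluster's allocation is known can differ between arms for reasons unrelated to the intervention. The conditions for that are present here. The SP alone decides who is eligible: a student qualifies if the SP sees at least one impairing symptom, and is left out if the SP thinks the student cannot attend, or would not benefit from, CBT skills groups. Coached SPs know their arm, because a coach visits weekly, and the coaching takes place in the SP's own CBT group. A coached SP may therefore choose students of different severity or motivation from those an uncoached SP would choose.

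A condition tied to listing before randomization would guard against this if it applied to students. Applied to schools, it guards only partly. With an average of at least 2 SPs per school, one early list qualifies the whole school. At stake are the exploratory PHQ-9T/GAD-7 comparison and the cost-effectiveness ratios that use depression- or anxiety-free days. Because the condition turns on whether a list came before or after randomization, a table that puts the two events in the opposite order from the text is also unhelpful.

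**Working it through.** **1. Does the figure the plan does give depend on this?** The article gives no sample size or power for the student analyses. Its one power statement concerns CBT sessions per SP: more than 80% power at D = 0.53, with 100 schools, 2 SPs per school, ICC 0.03 and phase 1 response rates of 10% and 50%. Taking the re-randomization adjustment as 1 + [(1 − 0.10) + (1 − 0.50)]/2 = 1.70, which is my reading of the described weighting:

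- SPs needed = 4(1.960 + 0.842)²/0.53² × (1 + 0.03) × 1.70 = 195.7, or 97.9 schools.
- Power at 100 schools = 80.8%.

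The stated figure is reproduced. It does not involve student lists, so the present point leaves it untouched.

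**2. What the Analyses rule excludes.** Take a school with two SPs.

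| SP A lists before randomization | SP B lists before randomization | School qualifies | Students listed later excluded by the stated rule |
|---|---|---|---|
| yes | yes | yes | no (later additions by either SP) |
| yes | no | yes | no (B's whole list, and later additions by A) |
| no | no | no | yes |

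The middle row is the weak one, and the wording anticipates it: a threshold of one SP is needed only if some qualifying schools have other SPs without an early list. Two further facts make it possible. Student outcomes only encourages listing and sets no closing date (Table 1 speaks of requiring it). Table 2 goes on counting students identified at each school in rows below the phase 1 randomization row.

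**3. How much late listing could there be?** The documents give no figure, so this is illustration only. Let q be the probability that an SP lists before randomization. Assume two SPs per school, independence between them, and that every SP who missed the date later submits a list of the same length. Among lists in qualifying schools:

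late share = 2q(1 − q) / {2[1 − (1 − q)²]} = (1 − q)/(2 − q)

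- q = 0.9: 0.1/1.1 = 9%
- q = 0.7: 0.3/1.3 = 23%
- q = 0.5: 0.5/1.5 = 33%

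These shares fall if SPs in the same school tend to list together (to zero if they always do) or if some late SPs never list. They leave out later additions by an SP who listed on time.

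**4. What would that do to the comparison?** If a share f of one arm's analysed students is listed late, and those students differ by d SD in baseline symptoms, the arm mean moves by f × d. For f from 5% to 50% and d from 0.1 to 0.5 SD, the shift runs from 0.05 × 0.1 = 0.005 SD to 0.50 × 0.5 = 0.25 SD. Both f and d are assumed. The range shows that the effect could be anything from negligible to material.

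**5. Order of events.**

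| Source | Order |
|---|---|
| Study design | identification in run-in, then phase 1 randomization |
| Student eligibility and recruitment | SPs trained in run-in to identify students |
| Student outcomes with Trial status | identification before and during training; training mid-January 2019; randomization late January 2019 |
| Table 2 | phase 1 randomization, training, receipt of lists, student assessments |

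Table 2 conflicts with the text on both training and listing.

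**The case against.** The strongest reply is that the planned timeline already deals with this. Four sections place identification in the run-in, and the dated one puts training, during which identification takes place, ahead of randomization. Late listing would be a departure from the plan, and the article nowhere says that late-listed students will be analysed. A reader might infer from the rule that such students do enter. The text does not support that: it only fails to exclude them, and Appendix 3, which is not shown, may hold a student-level cut-off. That part of the reply stands. It does not remove the point, because the article states a rule, its unit is the school, and its wording allows for SPs who had not listed in time.

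A reader might also take Table 2 literally and conclude that no list precedes randomization, so that the student analysis set would be empty. That does not follow. Table 2 is a fidelity checklist with a blank date column, it records when the database manager receives a list and not when the SP compiled it, and the dated statement in Trial status is better evidence. What remains is an inconsistency to be reconciled.

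Two further reservations stand. The article gives no reason for the restriction, so preventing selection after allocation is the natural inference but not a stated aim. And the primary aim section and Table 3 class student symptoms as exploratory, so the consequences are limited.

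**Conclusion.** The point holds in a limited form. The condition in Analyses works at school level and, as written, does not keep out students chosen after the arm is known. Because SPs select by judgement and coached SPs know their arm, identification bias is possible in the exploratory PHQ-9T/GAD-7 comparison and in the ratios per depression- or anxiety-free day. Its size cannot be derived from the documents; the shares and shifts shown above rest entirely on assumed inputs. The conclusion is about the rule as stated in the article, and a student-level cut-off in the unseen appendix would settle it. The primary outcome and its power are unaffected. Table 2's row order does conflict with the text, but it is evidence of inconsistent drafting and not evidence that lists will in fact be compiled after randomization.

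**What to change.** - Define the student analysis set as students named on a list received before the first randomization of their school.
- If listing dates can be linked only by SP, use students of SPs who had listed by then. This is weaker, because it still admits later additions by those SPs. The fallback may be needed: Measures says student information is de-identified at once, and the article does not show that a listing date can be tied to a survey.
- Report later-listed students separately, or add them only in a sensitivity analysis.
- Reconcile the order of rows in Table 2 (randomization, training, receipt of lists) with Study design, Student eligibility and recruitment, Student outcomes and Trial status.

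The cost is a sentence or two in the analysis plan, a listing date kept in the student registry, a reordered table, and somewhat fewer students in an exploratory analysis.
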